## Abstract

**Objective::**

Postoperative pulmonary complications are a series of disorders that can contribute to respiratory distress and prolonged mechanical ventilation postoperatively. We hypothesise that a liberal oxygenation strategy during cardiac surgery leads to a higher incidence of postoperative pulmonary complications than a restrictive oxygenation strategy.

**Methods::**

This study is a prospective, observer-blinded, centrally randomised and controlled, international multicentre clinical trial.

**Results::**

After obtaining a written informed consent, 200 adult patients undergoing coronary artery bypass grafting will be enrolled and randomised to receive either restrictive or liberal oxygenation perioperatively. The liberal oxygenation group will receive 1.0 fraction of inspired oxygen throughout the intraoperative period, including during cardiopulmonary bypass. The restrictive oxygenation group will receive the lowest fraction of inspired oxygen required to maintain arterial partial pressure of oxygen between 100 and 150 mmHg during cardiopulmonary bypass and a pulse oximetry reading of 95% or greater intraoperatively, but no less than 0.3 and not higher than 0.80 (other than induction and when the oxygenation goals cannot be reached). When patients are transferred to the intensive care unit, all patients will receive an initial fraction of inspired oxygen of 0.5, and then fraction of inspired oxygen will be titrated to maintain a pulse oximetry reading of 95% or greater until extubation. The lowest postoperative arterial partial pressure of oxygen/fraction of inspired oxygen within 48 hours of intensive care unit admission will be the primary outcome. Postoperative pulmonary complications, length of mechanical ventilation, intensive care unit stay, hospital stay, and 7-day mortality after cardiac surgery will be analysed as secondary outcomes.

**Conclusion::**

This is one of the first randomised controlled observer-blinded trials that prospectively evaluates the influence of higher inspired oxygen fractions on early postoperative respiratory and oxygenation outcomes in cardiac surgery patients using cardiopulmonary bypass.

Main PointsPostoperative pulmonary complications are a series of disorders that can contribute to respiratory distress and prolonged mechanical ventilation postoperatively.This is the study design of a prospective, observer-blinded, centrally randomised and controlled, international multicentre clinical trial to evaluate the influence of higher inspired oxygen fractions on early postoperative respiratory and oxygenation outcomes in cardiac surgery patients using cardiopulmonary bypass.Implementation of this clinical trial will help answer important questions on oxygen use in cardiac surgery.

## Introduction

Postoperative pulmonary complications (PPCs) include acute respiratory distress syndrome (ARDS), atelectasis, pulmonary oedema, aspiration, and pneumonia, which may lead to persistent lung injury, respiratory distress, and prolonged mechanical ventilation after surgery. Almost all patients undergoing cardiac surgery with cardiopulmonary bypass (CPB) develop some degree of postoperative pulmonary dysfunction, and 10%-25% patients develop PPCs.^1^ Postoperative pulmonary complications significantly worsen prognosis and result in prolonged recovery periods in the intensive care unit (ICU) and length of hospital stay.^2^ Although preoperative chronic obstructive pulmonary disease (COPD), smoking, anaemia, advanced age, and weakness impacted the incidence of PPCs, multiple intraoperative and postoperative factors such as mechanical ventilation, surgical manipulation, CPB, transfusion, lung recruitment manoeuvres, anaesthetic agents, and high-level fraction of inspired oxygen (FiO_2_) have been suggested as potential contributors to lung injury and PPCs.^3^

A postoperative protective or noninvasive mechanical ventilation strategy with low tidal volume [6 mL kg^–1^ ideal body weight (IBW)], lower driving pressures, and positive end-expiratory pressure (PEEP) is widely accepted as a key method for lung protection.^4^ However, intraoperative protective ventilation strategies are inconsistent and controversial during cardiac surgery, which suggests potential confounding factors may account for these results.^5^ Many critically ill cardiac surgical patients receive 1.0 FiO_2_ as a precaution to prevent hypoxia; thus, hyperoxia is common during cardiac surgery with a wide range of oxygen settings. Oxygen can directly and indirectly injure organs in 3 ways: (1) hyperoxia-related cardiovascular dysregulation, such as bradycardia and increasing vascular resistance; (2) direct tissue injury from increased production of reactive oxygen species (ROS); and (3) enhancement of ischaemia–reperfusion injury.^6^ Several clinical studies suggest that hyperoxia can cause myocardial injury, acute kidney injury (AKI), and neurologic dysfunction after cardiac surgery.^6^

Lungs can be adversely affected by hyperoxia as 1.0 FiO_2_ has been implicated in the development of atelectasis after even a short period. Prolonged ventilation with high concentrations of oxygen (FiO_2_ > 0.9) reliably causes severe hyperoxic acute lung injury and can be fatal when continued for extended periods. The severity of injury is proportional to both arterial partial pressure of oxygen (PaO_2_) (above 450 mmHg or FiO_2_ of 0.6) and duration of exposure.^7^ Hyperoxia during CPB was found to cause a greater decline in vital capacity and forced expiratory volume 5 days postoperatively when compared with normoxia.^8^ A retrospective analysis of 246 patients undergoing cardiac surgery with varying degrees of hyperoxia during mechanical ventilation (mild: PaO_2_ 100-199 mmHg, moderate: PaO_2_ 200-299 mmHg, severe: PaO_2_ > 300 mmHg) found that the group exposed to severe hyperoxia had more infectious complications, increased length of hospital stay, and increased time on mechanical ventilation after cardiac surgery.^9^ Another retrospective study consisting of 73 992 patients revealed that the median intraoperative FiO_2_ was associated with increased risk of respiratory complications and 30-day mortality.^10^ On the contrary, a retrospective study of 5056 patients found that intraoperative hyperoxia did not change the postoperative pulse oximetry reading (SpO_2_)/FiO_2_ ratio or the risk for pulmonary complications.^11^ Due to the contradictory nature of these retrospective studies, carefully designed prospective studies are needed to explore the relationship between FiO_2_ and PPCs after cardiac surgery. We hypothesise that a liberal oxygenation strategy during coronary artery bypass grafting (CABG) surgery leads to higher incidence of pulmonary complications than restrictive oxygenation strategy. The primary outcome is the lowest postoperative PaO_2_/FiO_2_ within the designated blood gas analysis testing periods in the first 48 hours of ICU admission comparing liberal (FiO_2_ 1.0) and restrictive intraoperative oxygenation (lowest FiO_2_ with adequate oxygenation) groups. Postoperative pulmonary complications, length of mechanical ventilation, ICU stay, hospital stay, and 7-day mortality after cardiac surgery will be analysed between liberal and restrictive oxygenation groups as secondary outcomes.

## Methods

### Study Design and Setting

This study is a prospective, observer-blinded, web-based centrally randomised, controlled, multicentre, international clinical trial to assess the relationship between intraoperative FiO_2_ and PPCs. Surgical technique will be restricted to CABG with CPB through median sternotomy to minimise variation. Arterial partial pressure of oxygen/FiO_2_ will be assessed at baseline (preoperative values), time of postoperative ICU admission as well as 4 hours, 8 hours, 12 hours, 18 hours, 24 hours, 36 hours, and 48 hours after postoperative ICU admission (Figure 1). The study will be conducted at University of Louisville Health, Louisville, KY, USA, and 5 teaching hospitals from China with a combined more than 8000 open-heart surgeries and over 1000 CABG with CPB cases per year. We have been assured fair access to research subjects to enable completion of this study within a 1-year period. Written informed consent will be obtained from each participant preoperatively.

This study is designed not to interfere with routine clinical workflow, and patients will be centrally randomised to either restrictive or liberal oxygenation groups in a 1 : 1 ratio, and the randomisation will be stratified for each centre. For blinding, the research fellows and ICU physicians who record and assess the primary and secondary outcomes as well as who manages the patients will be blinded to the randomisation group assignment. The principal investigator (PI) of each centre and the physicians who conduct the anaesthesia and monitoring intraoperatively in the operating room are unblinded due to necessary requirements for clinical care. This protocol is in accordance with the Recommendations for Interventional Trials (SPIRIT) checklist. The SPIRIT figure demonstrates the schedule of enrolment, interventions, and outcome assessment of this trial (Table 1).

### Study Registration

The Institutional Review Board (IRB) at the University of Louisville approved the study protocol for University of Louisville sites and provides ongoing oversight (IRB 19.0988). All sites from China will obtain approvals from local IRBs. Data sharing agreements will be obtained from these study sites. This study was registered at ClinicalTrials.gov on 3 October 2019 (NCT04115501). The trial has not begun recruitment pending IRB approval from Chinese sites. All amendments to this protocol will be reported to the IRB of University of Louisville as well as the relevant IRBs of involved study sites.

### Inclusion and Exclusion Criteria

The study will enrol adult patients aged 18-80 with a body mass index (BMI) from 20 to 39.9 who are undergoing isolated CABG with CPB support through median sternotomy with subsequent admission to an ICU. Patients with severe COPD (i.e., Forced expiratory volume in 1 second (FEV_1_) < 50% and preoperative PaCO_2_ > 60 mmHg) will be excluded. Pregnant women will be excluded. Patients with recent acute coronary syndromes (<1 week), acute onset of heart failure, severe anaemia (haemoglobin < 8g dL^–1^), preoperative supplemental oxygen to maintain oxygen saturations (SpO_2_) above 90%, right to left intracardiac shunts, unresolved carotid stenosis defined as >50% stenosis of either carotid artery, end-stage renal disease requiring dialysis, recent smoking (within 1 week), and planned regional anaesthesia will be excluded (Table 2).

### Intervention and Anaesthetic Regimen

Anaesthesia will be induced with a combination of sufentanil (1-4 μg kg^–1^) or fentanyl (2-10 μg kg^–1^), propofol (1-3 mg kg^–1^) or etomidate (0.2-0.3mg kg^–1^), and succinylcholine (1-2mg kg^–1^) or rocuronium (1-2 mg kg^–1^). General anaesthesia will be maintained with sevoflurane or isoflurane (Minimum alveolar concentration [MAC] 0.5-1.5). Additional narcotics and muscle relaxants will be used at the discretion of attending anaesthesiologists before and after CPB. The total dose of sufentanil is not to exceed 15 μg kg^–1^ and the total dose of fentanyl is not to exceed 10 μg kg^–1^, and only 1 narcotic will be used for any single case. Train of 4 will be monitored during the entire case to adjust the dosage of muscle relaxants. Arterial blood gas (ABG) will be obtained in the pre-anaesthesia clinic while breathing room air, after anaesthesia induction but before CPB, on CPB, after CPB, and other clinically indicated time points during cardiac surgery to adjust FiO_2_ in the restrictive oxygenation group. While the patient is on CPB, anaesthesia circuits will be disconnected and lungs will be exposed to the atmosphere. Before coming off CPB, recruitment manoeuvre will be performed to inflate lungs. When the patient is transferred to the ICU, ABG analysis will be performed on admission and at 4 hours, 8 hours, 12 hours, 18 hours, 24 hours, and 48 hours after ICU admission. Tidal volume will be set at 6-8 mL kg^–1^ IBW, respiratory rate to maintain normocapnia, PEEP will be managed between 5 and 10 cm H_2_O at the discretion of the intensivist, and I : E ratio between 1:1.5 and 1:2.

Postoperative pain management will be provided as a bolus of 25 μg fentanyl, 0.2 mg hydromorphone intravenously, a continuous opioid infusion as needed, or 5-10 mg hydrocodone or oxycodone with acetaminophen orally with the aim of a visual analogue score less than 4. The goal is to achieve adequate pain control without respiratory compromise. Only normal saline, lactated Ringer’s solution, human albumin, or cell saver blood are allowed as maintenance infusion fluids during and after surgery. Fluid infusion rate from CPB weaning until the end of surgery should be less than 10 mL kg^–1^ h^–1^ to avoid pulmonary oedema; otherwise, the patient will be withdrawn from analysis. The trigger for transfusion of allogeneic red blood cells is 7 g dL^–1^ during CPB and 8 g dL^–1^ while not on CPB. The trigger for transfusion of plasma, cryoprecipitate, and platelets is determined by the laboratory values and clinical protocols. Transfusion of more than 2 units of red blood cells (RBCs), fresh-frozen plasma, platelets, or cryoprecipitate within 48 hours of ICU admission will result in withdrawal from the study.

After anaesthesia induction and intubation, the restrictive oxygenation group will have FiO_2_ set at a minimum of 0.3 to maintain SpO_2_ greater than or equal to 95%. If the SpO_2_ is above 95%, a 10% further reduction in FiO_2_ will be attempted to achieve the lowest possible FiO_2_ while maintaining an SpO_2_ > 95%. During CPB, a blended air/oxygen mixture will be titrated to ABG results with the goal of PaO_2_ between 100 and 150 mmHg. The liberal oxygenation group receives 1.0 FiO_2_ throughout the intraoperative period, including during CPB. After admission to ICU, all patients will receive 0.5 FiO_2_ initially and then titrated to the lowest FiO_2_ while maintaining SpO_2_ ≥ 95% until extubation. Criteria for sedation weaning include a stable heart rate and blood pressure and a chest tube output < 200 mL over the last 2 hours. Criteria for mechanical ventilation weaning trial include a rapid shallow breathing index <100, a respiratory rate < 35, an SpO_2_ > 92%, a heart rate < 140 bpm, a systolic blood pressure <180 mmHg and >90mmHg, and no anxiety or diaphoresis from increased work of breathing. Goal-directed extubation criteria will be utilised in the cardiac ICUs of study centres. These criteria include an FiO_2_ ≤ 0.40, an SpO_2_ ≥ 95%, a rapid shallow breathing index < 100, and a negative inspiratory force ≥ –20cm H_2_O. Postoperative narcotic analgesia and sedation approaches are standardised to minimise the discrepancies among the centres. After extubation, the patient may still need continuous oxygen support in the ICU or after ICU discharge, and the lowest SpO_2_/FiO_2_ ratio will be recorded daily until discharge from the hospital.

### Safety Assessment

The PI, investigators, study coordinators, attending anaesthesiologists, and intensivists will be in close communication throughout the entire procedure until patient discharge to ensure protocol adherence. Patients will be withdrawn intraoperatively if they require 1 lung ventilation, additional procedures other than CABG, circulatory arrest, repeated episodes of CPB support, or usage of circulatory assist devices. If a patient suffers an SpO_2_ < 90% for more than 5 minutes at any time during the surgery, the patient will be withdrawn, and this will be recorded as a serious adverse event. Postoperatively, if a patient experiences delayed extubation (i.e., weaning/extubation period lasting longer than 48 hours) or requires reintubation for non-respiratory reasons (i.e., surgical reasons), suffers major bleeding (i.e., requiring a delay in extubation due to haemodynamic management), and develops heart failure, they will be withdrawn. If there is a perioperative allogenic RBC transfusion of more than 2 units or if a patient receives any other blood products, the patient will also be withdrawn (Table 2). Other postoperative events such as AKI, stroke, myocardial infarction, reoperation, and sternal wound infection will be recorded as adverse events and be analysed to determine whether they are related to the intervention. A trained research team member (i.e., fellow, study coordinator) will monitor the protocol compliance and report any adverse events to the IRB.

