### Data Analysis

Data will be expressed as mean ± SD or median (minimum and maximum) and percentage as appropriate for continuous and categorical variables, respectively. A *t-*test will be used to compare continuous variables. For comparison of ratio or ordinal categorical data, the Pearson chi-squared test (or Fisher’s exact) or a Mann–Whitney *U*-test will be used. Two-sided *P-*values less than .05 will be considered statistically significant. All the analyses will be conducted using the R software.

The primary outcome of the study is the lowest PaO_2_/FiO_2_ within 48 hours after ICU admission between liberal and restrictive oxygenation groups. A non-parametric equivalent *t-*test will be used to compare groups. The percentage of shift from baseline will also be calculated and compared by the *t-*test. The ratio of shift over 10% from the baseline of each group will be compared by the chi-squared test. Secondary outcome analysis of PPC incidence and mortality of the groups will be compared by the chi-squared test. Odds ratios or measures of relative risk will include 95% CIs. Secondary outcomes including the length of mechanical ventilation and lengths of postoperative ICU and hospital stay will be calculated and compared by a *t-*test.

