The major limitation of this study lies in the difficulty of balancing many confounding factors during CABG with CPB that are harmful to the lungs, including the surgical procedure, CPB, hypothermia, blood contact with artificial surfaces, ischaemia–reperfusion injury, administration of blood products, and lung collapse.^21^ In our protocol, if the patient develops haemodynamic instability which requires a return to CPB or suffers circulatory arrest, they will be withdrawn from the study. We will also withdraw patients who require mechanical circulatory support systems like extracorporeal membrane oxygenation, ventricular assist device, or an Impella device for similar reasons. Transfusion is common in cardiac surgery, but CABG has a relatively low transfusion rate compared to other open-heart surgeries.^22^ Transfusion-associated lung injury (TRALI) has been well defined, and it is a prominent factor for increased morbidity and mortality.^23,24^ The reported incidence of TRALI varies widely, ranging from 0.0008% to 1.2% per unit of blood product administered and from 0.08% to 8% per transfused patient.^25^ Since transfusion of blood products, in particular blood plasma, may cause lung injury, these patients will also be withdrawn from our analysis. We predict a high rate of withdrawal, not only for safety reasons but also for bias control and balancing of confounding factors. Another study limitation is our inability to blind the anaesthesiologist. Only ICU physicians and research fellows/study coordinators who assess the outcomes will be blinded.

There exists increasing evidence that a restrictive oxygenation strategy may be beneficial in various groups of patients.^26^ It is important to understand the relationship between FiO_2_ and lung injury after cardiac surgery. This is one of the first randomised controlled trials to prospectively evaluate the influence of high inspired oxygen concentrations on pulmonary outcomes and oxygenation after cardiac surgery.

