## Figures and Tables

**Figure 1. f1-tjar-51-2-112:**
[figure not shown]
Algorithm and timetable for enrolment, allocation to restrictive or liberal oxygenation groups, intraoperative management, and postoperative data collection.

**Table 1. t1-tjar-51-2-112:** The Schedule of Enrolment, Interventions, and Outcome Assessment in Different Periods of This Trial

	Enrolment	Allocation	Post-allocation			Close-out
Timepoint	Preoperative 1 Day Before Surgery	Before Oxygenation	Intraoperative	Postoperative 0 hours, 4 hours, 8 hours,12 hours, 24 hours, 48 hours	Discharge	Postoperative 7 Days
Enrolment						
Eligibility screen	**X**					
Informed consent	**X**					
Allocation		**X**				
Interventions						
Restrictive oxygenation group			**X**			
Liberal oxygenation group			**X**			
Assessments						
PaO_2_/FiO_2_ (ABG)		**X**	**X**	**X**		
Postoperative pulmonary complications				**X**	**X**	
Length of mechanical ventilation					**X**	
ICU stay					**X**	
Hospital stay					**X**	
Mortality						**X**

ABG, arterial blood gas; ICU, intensive care unit.

**Table 2. t2-tjar-51-2-112:** Inclusion, Exclusion, and Withdrawal Criteria

Inclusion and Exclusion Criteria	Withdrawal Criteria
Inclusion criteria	Preoperative
Age from 18 to 80 BMI from 20 to 39.9 Isolated CABG CPB planned Median sternotomy approach Subsequent admission to ICU	Onset of heart failure Onset of acute decompensated arrhythmia Onset of low oxygen saturation (SpO_2_ < 90%) on supplemental oxygen
Exclusion criteria Severe COPD (PaCO_2_ > 60 mmHg) Recent acute coronary syndrome (<1 week) Acute onset of heart failure Severe anaemia (haemoglobin < 8 g dL^–1^) Preoperative supplemental oxygen required to maintain SpO_2_ >90% Right to left intracardiac shunts Carotid stenosis defined as >50% stenosis of either carotid artery End-stage renal disease requiring haemodialysis Recent smoking (within 1 week) Planned regional anaesthesia	Intraoperative One lung ventilation Additional procedures other than CABG CPB more than once or circulatory arrest Fluid infusion rate more than 10 mL kg^–1^ h^–1^ post CPB Patients in restrictive oxygenation group needing FiO_2_ > 0.7 to maintain SpO_2_ ≥95% SpO_2_ < 90% lasting for more than 5 minutes
	Postoperative Non-respiratory reasons to reintubate Delayed extubation due to bleeding Delayed extubation due to heart failure	Any time Allogenic transfusion except less than 2 units RBC Circulatory assist device implantation (ECMO, VAD, or Impella^®^ device)

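### The Safety Assessment withdraws patients for a weaning/extubation period above 48 h with no cause stated, Table 2 only for bleeding or heart failure; the text version would exclude patients on the upper tail of an outcome

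*Protocol article*

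**What the plan says.** The article states the withdrawal rule for slow extubation in two places.

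- **Safety Assessment (text):** a patient is withdrawn "if a patient experiences delayed extubation (i.e., weaning/extubation period lasting longer than 48 hours"). No cause is named. The next item in the same sentence does carry a limit: withdrawal applies if the patient "requires reintubation for non-respiratory reasons (i.e., surgical reasons"). Major bleeding that delays extubation and heart failure follow as further items.
- **Table 2, postoperative withdrawal criteria:** "Delayed extubation due to bleeding Delayed extubation due to heart failure". There is no 48 h limit and no entry for delay from other causes.

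On what withdrawal means, the fluid rule under Intervention and Anaesthetic Regimen says "otherwise, the patient will be withdrawn from analysis". The Discussion says of transfused patients that "these patients will also be withdrawn from our analysis", and adds: "We predict a high rate of withdrawal, not only for safety reasons but also for bias control and balancing of confounding factors". The Sample Size Calculation raises 160 to 200 partly to cover withdrawal.

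Under Secondary Endpoints, the outcomes include a composite of pulmonary complications (PPCs), duration of ventilation, and ICU and hospital stay. Data Analysis states: "Secondary outcomes including the length of mechanical ventilation and lengths of postoperative ICU and hospital stay will be calculated and compared by a" t-test.

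**The concern.** A patient who cannot be extubated because the lungs are injured is withdrawn under the text and retained under the table. Sites cannot apply both.

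The text version has a statistical cost. It selects patients on an event that occurs after randomisation, may be caused by the allocated oxygen strategy, and forms the upper end of a named outcome. The Introduction says PPCs are disorders "which may lead to persistent lung injury, respiratory distress, and prolonged mechanical ventilation after surgery". The Discussion places ventilator-induced injury and ventilator-associated pneumonia mainly in patients ventilated beyond 48 h. So, by the article's own account, the rule would take out patients in whom these events concentrate.

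What remains would no longer be a randomised comparison. Harm from liberal oxygen that shows as more patients ventilated beyond 48 h would be hidden in ventilation time, ICU stay, hospital stay and PPCs. The comparison of the lowest PaO2/FiO2 could also be biased. A larger sample would not cure this.

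**Working it through.** The article gives no figure for this rule, so there is none to reproduce. The check compares the passages and then illustrates the size.

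**1. The two rules side by side**

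| Patient | Safety Assessment | Table 2 |
|---|---|---|
| Period above 48 h, respiratory cause | withdrawn | stays |
| Period above 48 h, bleeding or heart failure | withdrawn | withdrawn |
| Reintubated for a respiratory reason | stays | stays |

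The first row is the contradiction.

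**2. Does withdrawal mean leaving the analysis?** It is explicit for fluid and for transfusion. The sample size treats withdrawal as loss: 1 − 160/200 = 20% allowance for withdrawal, protocol violation and loss to follow-up together. For delayed extubation it is an inference. It is a strong one, because the randomised strategy is intraoperative and ICU oxygen is managed alike in both groups, so a postoperative withdrawal has no allocated treatment left to stop.

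**3. What an effect confined to the tail does.** Let p_R and p_L be the shares above 48 h, m the mean time of all other patients (the same in both arms), and M the mean time of those above 48 h.

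- All patients kept: difference in means = (p_L − p_R) × (M − m).
- Patients above 48 h removed: difference = m − m = 0.

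Assumptions, none from the documents except that usual extubation is within 6 h (Discussion): p_R = 4%, p_L = 10%; other times log-normal with median 6 h and log-SD 0.5; long times 48 h plus a log-normal excess with median 48 h and log-SD 0.7.

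- m = 6 × exp(0.5²/2) = 6.80 h
- M = 48 + 48 × exp(0.7²/2) = 48 + 61.33 = 109.33 h
- Difference, all kept = 0.06 × (109.33 − 6.80) = 6.15 h
- Difference after removal = 0 h

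In simulation with 100 per arm, the two-sided t-test at 0.05 rejects in about 0.33 of trials with everyone kept and 0.05 after removal, which is chance level. On average the rule removes 4 + 10 = 14 of 200 patients.

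**4. Other assumed rates.** Here the other times are log-normal with median 6 h and log-SD 0.6, and long times are 48 h plus an exponential excess of mean 72 h (4,000 simulated trials, 100 per arm).

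| Above 48 h, restrictive v liberal | Difference, all kept | t-test rejection, all kept | Difference, removed | t-test rejection, removed |
|---|---|---|---|---|
| 3% v 3% | 0.0 h | 0.03 | 0.0 h | 0.05 |
| 2% v 6% | 4.5 h | 0.22 | 0.0 h | 0.05 |
| 3% v 9% | 6.8 h | 0.35 | 0.0 h | 0.05 |
| 5% v 15% | 11.4 h | 0.54 | 0.0 h | 0.04 |
| 5% v 20% | 16.9 h | 0.80 | 0.0 h | 0.05 |

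The formula agrees: for 3% v 9%, m = 6 × exp(0.6²/2) = 7.18 h, M = 48 + 72 = 120 h, and 0.06 × 112.82 = 6.77 h.

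**The case against.** The strongest reply is that the Safety Assessment sentence is loosely built. The non-respiratory qualifier might be meant to cover delayed extubation as well as reintubation, and that section points to Table 2, which keeps respiratory delays in. On that reading patients with lung injury are not lost. This stands as far as it goes: a reader might infer that every patient not extubated by 48 h is certainly removed, and the documents do not settle that. But the sentence lists bleeding-related delay as a separate item, which would be largely redundant if the 48 h item were already limited to such causes. The conflict is real and needs resolving.

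Three further points stand.

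- The start of the weaning/extubation period is not defined, so the rule cannot be read as a cut at exactly 48 h after ICU admission.
- The fall to 0 h follows by construction from making the arms identical at or below 48 h. It shows what is lost for an effect confined to the tail. A shift within 48 h, and respiratory reintubations, would still be seen.
- The effect on the lowest PaO2/FiO2 is not quantified. One might infer that the primary outcome simply loses its lowest values; the documents give nothing to establish that.

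A reader might also conclude that the t-test on skewed times is at fault and should give way to a rank test. That does not follow. The t-test is not what hides the effect, and its rejection rate with equal arms stayed at or below about 5%. Which test is better depends on the form of the effect: for a tail-only effect with everyone kept (3% v 9%), the t-test rejected more often than the Mann-Whitney test (0.35 v 0.12).

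**Conclusion.** The concern holds in limited form. The Safety Assessment and Table 2 give incompatible withdrawal rules for delayed extubation. Under the text version, and on the meaning of withdrawal used elsewhere in the article, patients would be excluded on a post-randomisation event that is the upper tail of a secondary outcome and a likely consequence of PPCs.

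Across the assumed scenarios, true mean differences of 4.5 to 16.9 h become 0 h, and rejection rates of 0.22 to 0.80 fall to about 0.05. These sizes rest on assumed tail rates and on identical arms below 48 h. That such an effect is hidden does not depend on the particular rates. Removal from the analysis is inferred for this rule, not stated. The documents do not support the stronger conclusion that any prolonged-ventilation harm would disappear, nor a case for changing the test.

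**What to change.** 1. Reconcile the Safety Assessment section with Table 2 so that one rule for delayed extubation stands, and define when the weaning/extubation period starts. Which clinical rule applies is for the investigators.
2. Whatever that rule is, state that delayed extubation is not a reason to leave the analysis. Continue to collect outcomes and analyse these patients in their randomised group for all outcomes.
3. Use exclusion of these patients only as a labelled sensitivity analysis.

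The cost is wording. If the weaning period cannot start before ICU admission, the scheduled 48 h blood gas is already due when the rule is met, and ventilation time, stays and 7-day status are planned data. The article says recruitment had not begun, so the change can be made as an amendment before any patient is affected.
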